### Sample Size and Recruitment

It is intended to recruit 154 participants (77 women). This sample size was calculated using a power analysis involving *G*Power 3.1* [58], with an additional 20% added to compensate for possible dropouts.

The recruitment will be done by flyer distribution in the University of Konstanz, as well as an entry in an online platform where experiments are offered by the departments of psychology and linguistics.

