**Methods:**

We aim to collect data from 308 participants recruited at our local university. Participants’ social motives are assessed using a standardized measure in motive research (Picture Story Exercise). Then, the Trier Social Stress Test for Groups (TSST-G) is used to experimentally induce psychosocial stress. One group of participants receives social support from an associate of the experimenter, while the control group does not receive social support. Stress responses will be assessed by a modified version of the state anxiety scale of the State–Trait Anxiety Inventory and by physiological indicators of stress (cortisol and α-amylase from saliva samples) at 7 measurement points. Reproductive hormones will be analyzed in 4 of these 7 saliva samples. Heart rate and heart rate variability will be assessed continuously. We will additionally measure participants’ performance in an interview (part of the TSST-G) using a self-developed categorization system.

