### Study Design

The study is based on a mixed within- and between-subject design. The within-subject factors are participants’ stress responses (self-reports and biological markers) across the steps of the TSST procedure (Figure 1). The between-subject factors are experimental groups (social support vs no social support), social motives, and participants’ sex. GRSC and other control variables will be assessed as controls and entered as covariates into the analysis models. Allocation will be based on a 1:1 ratio. There will be no cross-over into the experimental group.

The study will be conducted in the laboratory of sports psychology of the Department of Sport Science at the University of Konstanz, Germany. The analyses of hormones and α-amylase will be performed in the biochemical laboratory of the Institute for Medical Psychology in Heidelberg, Germany.

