### Statistical Analysis

Statistical analysis will be performed using IBM SPSS Statistics, Version 28 (IBM Corp) for Windows (statistical analysis and graphs). We will perform an analysis of variance with repeated measures to determine if the TSST procedure results in significant increases in psychological and biological variables for all participants. We will calculate multiple linear regressions to examine interaction effects. In these regressions, we will first include the control variables, then the condition as a dummy variable, and finally the individual predictors and their interaction terms. To account for repeated measurements of the collected hormones, the area under the curve with respect to increase will be calculated and used as a dependent variable [71]. As an additional effort to ensure that participants with a delayed significant increase in their hormones will not be excluded, an adjusted increase value will be calculated, regardless of the time of measurement. This value will be obtained by subtracting the baseline value from the peak value. Multiple regressions will be calculated again with these adjusted values. Nonbiological dependent variables, such as those obtained from the psychological test battery, will be added as means. Only data from individuals who have fully completed the TSST protocol will be included in the final analyses. Missing data will be added by multiple imputation.

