#### Description of Interim Analysis and Stopping Guidelines

No interim analysis or guidelines for study termination are provided. Data collection will cease when the target sample size is reached.

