## Results

The Ethics Committee of the University of Constance approved the application to conduct the study on December 18, 2018. The start of the experiment was planned for the beginning of 2019 but was postponed to June 2021 due to COVID-19. The protocol version is dated May 22, 2022. Data collection will take place until the end of 2022. Publication of the initial results is planned for spring 2023.

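### The target sample size is 308 in the abstract and 154 in the Methods, so the sample-size stopping rule and the detectable effect are each ambiguous between two values.

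*Protocol article*

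**What the plan says.** The article gives the planned sample size twice.

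- Abstract, Methods paragraph: "We aim to collect data from 308 participants recruited at our local university".
- Methods, Sample Size and Recruitment: "It is intended to recruit 154 participants (77 women" among them). This number is said to come from a G*Power calculation, "with an additional 20% added to compensate for possible dropouts".

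Three other statements bear on how these numbers are read.

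- Study Design: "Allocation will be based on a 1:1 ratio".
- Description of Interim Analysis and Stopping Guidelines: "No interim analysis or guidelines for study termination are provided", followed by "Data collection will cease when the target sample size is reached". No number is given there.
- Results: "Data collection will take place until the end of 2022".

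For the moderation hypotheses, the Statistical Analysis section says "We will calculate multiple linear regressions to examine interaction effects" and restricts the final analyses to participants who completed the whole stress-test protocol.

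**The concern.** Both statements are current text, and they cannot both be the total. The sample size decides when recruitment ends and how small a support-by-motive interaction the study can find. The stopping rule refers to a target that has two published values, so ending at 154 and ending at 308 would each agree with one part of the article. A reader of the eventual results could not tell whether the study reached its plan, stopped at half of it, or ran to twice it. A null moderation result would also carry different weight in each case, and moderation is the study's main question.

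**Working it through.** **1. The two totals.** 308 / 154 = 2 exactly, and 308 = 4 × 77.

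- If 154 is the total, there are 77 women and 77 men. With 1:1 allocation that is 77 per condition, or 77 / 2 = 38.5 (38 or 39) per sex within each condition.
- If 154 is per condition, the total is 2 × 154 = 308, with 77 women and 77 men in each condition.

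Both readings are arithmetically possible. The Sample Size section attaches no per-group or per-sex qualifier to 154, so its plain reading is a total of 154, which contradicts the abstract.

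**2. Can the stated number be reproduced?** Not from the article, which gives no effect size, alpha, power or test. Under conventional inputs that I assume (two-group t-test, d = 0.5, two-sided 5%, 80% power), the requirement is 64 per group, or 128 in total. Then 128 × 1.2 = 153.6, which rounds to 154. This fits 154 as a total but does not prove it. A 1-df regression test at f² = 0.0625 also needs 128. A base of 123 inflated by division gives 123 / 0.8 = 153.75, which also rounds to 154.

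**3. Plausible numbers analysed under each target.** The lower end takes 20% off the recruited number. The upper end removes the added 20%.

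- Target 154: 154 × 0.8 = 123.2 and 154 / 1.2 = 128.3, so about 123 to 128.
- Target 308: 308 × 0.8 = 246.4 and 308 / 1.2 = 256.7, so about 246 to 257.

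**4. Detectable interaction.** Assumptions: one interaction term tested with 1 df, two-sided 5%, and 8 predictors in the model. With N analysed, the test statistic follows a noncentral F with 1 and N − 9 degrees of freedom and noncentrality f² × N. The second column is the f² that gives 80% power.

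| N analysed | Detectable f² | Power at f² = 0.02 | Power at f² = 0.05 |
|---|---|---|---|
| 123 | 0.065 | 34% | 69% |
| 128 | 0.062 | 36% | 71% |
| 246 | 0.032 | 60% | 94% |
| 257 | 0.031 | 62% | 95% |

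Using 6 predictors instead of 8 leaves the detectable f² unchanged to the digits shown.

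**5. Detectable group difference.** For a simple two-group comparison with the same alpha and power, the detectable standardised difference is 0.51 to 0.50 for 123 to 128 analysed, and 0.36 to 0.35 for 246 to 257. The ratio is about √2, as expected when N doubles.

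**The case against.** The strongest reply is that this may be a slip in the abstract. The Methods number is the more detailed one, carries a sex breakdown and a stated origin, and fits a conventional total. The calendar end also limits recruitment whichever number applies. This makes 154 the likelier reading, but it does not remove the contradiction. Neither the calendar date nor any other sentence says which total is meant, and a fuller document could not make both numbers correct.

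Several stronger conclusions are tempting, and the article does not support them.

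- *Type I error is compromised.* A single test at 5% keeps 5% at either fixed N. Testing at 154 and again at 308 without adjustment would give about 8.3%, but the plan provides for no interim analysis and nothing says such a look will occur.
- *The investigators may choose the stopping point after seeing results.* The Data Monitoring section says the two principal investigators are in close contact about the data, as the reason for having no separate committee. That is no evidence that outcomes are compared by condition during recruitment.
- *The 20% allowance was applied the wrong way round.* This needs a base of 128, which the article does not state. A base of 123 divided by 0.8 reaches 154 as well. Adding 20% for possible dropouts also does not assert that 20% will be lost.
- *The base N and the powered test are missing.* These may stand in the full study protocol, which is listed as an appendix and not shown here, so their absence from an article is not an error.

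**Conclusion.** The contradiction is real and wrong as written: one of the two totals must be incorrect or incompletely described. The stopping rule exists, but its sample-size limb is ambiguous by a factor of two in N. The detectable interaction is correspondingly ambiguous, with f² about 0.06 under 154 and about 0.03 under 308. For an interaction of f² = 0.02, power is roughly 34 to 36% under the first target and 60 to 62% under the second.

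The f² and power figures rest on my assumed test, alpha, power, number of predictors and completion rates, none of which the article gives. They show how much the choice matters and do not reconstruct the plan's own calculation. The factor of two between the stated totals rests on no assumption.

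**What to change.** - State one total N, with its breakdown by condition and sex, and use it in the abstract and the Sample Size and Recruitment section. Write the number into the stopping rule.
- Say explicitly whether 154 is the total or the number per condition.
- Check that the G*Power calculation referred to in the Sample Size section corresponds to the number kept.
- State how that number and the end-of-2022 date work together, that is, which one ends data collection if they disagree.

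If the intended number is confirmed, the cost is a few sentences and no additional participants.

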### Eligibility Criteria

The following primary criteria must be fulfilled to participate in the study: (1) informed consent for all aspects of the study (agreement with video recording and hormone collection); (2) age at least 18 years; and (3) ability to speak German as the native language.

Participants who meet the following exclusion criteria will be excluded from study participation: (1) previous participation in stress experiments, as well as psychology and sports students from the 5th semester and (2) presence of physical or mental illness, nicotine consumption, drug use, BMI of 30 or more, and regular use of medication (including hormonal contraception), as these could influence the physiological stress response [59].

### Participant Adherence

Participants will receive €40 (about US $42) payment at the end of the laboratory session independent of whether or when participants decide to discontinue the study. To promote participant adherence with the appointment and study protocol, they will receive a reminder email after having filled in the web survey and 1 day before their laboratory appointment.

### Procedure

#### Web Survey Prior to the Laboratory Session

The participants complete an online questionnaire (Limesurvey) at home. Here, the eligibility criteria are checked, the implicit motives are assessed by using the Picture Story Exercise (PSE) [60], and GRSCs [61], as well as other control variables, are measured. The exercise and sports activity questionnaire [62] will be administered to test a related but different research question (Multimedia Appendix 1). Participants, who are eligible for the study, will be invited to the laboratory session via email. Participants confirm their agreement that they will be contacted by email and learn that email addresses will be deleted after the appointment is made.

#### Laboratory Session

Figure 1 shows the schematic procedure of data collection. It starts with a general preparation phase, where the baseline measurements of physiological parameters (hormones), control variables, and psychological variables (self-reports about well-being, stress experience, and motive-specific affect) take place. In the preparation phase for the TSST-G, the participants prepare for the task. The participants in the experimental group receive social support during this phase, while the participants in the control group do not receive any social support. Finally, there will be a 45-minute rest period during which repeated physiological and psychological questionnaires will be completed. A detailed procedure is provided in Multimedia Appendix 3.

#### General Preparation Phase

In each laboratory session, 3 participants will arrive between 5:00 and 5:15 PM outside the laboratory and will be led individually to their own preparation room (so that they cannot contact each other). First, they will be asked to read the study information sheet again and then will provide their written consent (Multimedia Appendix 2). Afterwards, the participants will generate their participant code via paper and pencil format, which ensures that the saliva samples, as well as other collected data, can be stored anonymously. Then, they will complete a short day-screening questionnaire (Multimedia Appendix 4) on a computer, which will assess control variables (eg, sports, medication intake, smoking, and caffeine and alcohol consumption). Afterward, they will be asked to wear a pulse belt that contains a Polar H10 sensor (Polar Electro). When putting on the belt, the experimenter will leave the room. After that, the participants will provide an initial saliva sample at measurement time T0 (−11 min) and will complete the first test battery, including different questionnaires, on a computer (hereafter referred to as psychological questionnaires).

#### Preparation Phase of the TSST-G Without Social Support

For the preparation phase, each participant sits in a separate room. Here, they receive written instructions for the upcoming interview (Multimedia Appendix 5). After they have had 10 minutes of preparation time for this task, they give a saliva sample (T1, 0 min) and complete the psychological questionnaire again. Subsequently, the participants are individually led to their places in front of the panel.

#### Preparation Phase of the TSST-G With Social Support

The preparation phase is identical to the described scenario for the participants without social support, with the exception that the experimenter introduces a female associate as a student assistant who can assist the participants if needed. The female associate provides passive social support for the first 5 minutes, ostensibly working on the computer. In the second 5 minutes of the preparation phase, the associate gives active social support and also notes the reactions of the participants (Multimedia Appendix 6). At the end of the 10-minute preparation period, the associate asks the participants for a saliva sample (T1, 0 min) and tells the participants to complete the psychological questionnaire again. Then, rooms are changed. All other instructions are the same as in the group without social support.

#### TSST-G

##### Psychosocial Stress Induction

Our procedure is based on the TSST-G developed by Von Dawans et al [49]. Each participant is required to present his or her interview individually in front of the panel for 3 minutes at a time. During this time, the participant is interrupted in a standardized manner by the panel (Multimedia Appendix 7). After that, they give a saliva sample (T2, +12 min) and complete the psychological questionnaire. Subsequently, each participant has to perform the arithmetic task 3 times for 30 seconds. When this task is finished, they give another saliva sample (T3, +20 min). During this whole procedure, the participants are recorded with a microphone and a camera. The experimenter then leads the participants individually from the TSST-G test room to the respective preparation rooms. Here, they again fill in the psychological questionnaire.

##### Rest Phase

During the rest period, 3 additional saliva samples are collected (T4, +30 min; T5, +45 min; T6, +65 min). Participants who have received social support will complete a social support scale at T6 (+65 min) (Multimedia Appendix 8).

##### Debriefing

Finally, the experimenter leads all subjects to the TSST-G testing room and provides a debriefing about the aim of the study (Multimedia Appendix 9). Questions are answered as needed. The participants receive their payment and are dismissed.

### Manipulation Check of Social Support

To check whether social support was received as such by the participants, a modified version of the received support subscale of the Berlin Social Support Scale [63] will be used (Multimedia Appendix 8; T6, +65 min). Item wording is adapted to the study context. Two items from the original scale are deleted because they refer to instrumental support, and the social support in this study rather refers to emotional and informal social support. The item “This student assistant was there for me when I needed her” is also counted as instrumental support according to Schulz and Schwarzer [63], but it can also be understood as emotional support and therefore remains included. Items are rated on a 4-point Likert scale ranging from 1 (not true) to 4 (exactly true). The original version of the received support scale has good internal consistency (α=.83). In addition, participants will be asked directly whether they received support from the student assistant and whether they found this support helpful.

### Test Battery of Psychological Questionnaires

Participants are asked to complete the psychological questionnaire a total of 7 times (Figure 1).

Well-being will be captured via 6 items (short version A) from the Multidimensional Well-Being Questionnaire (MDBF) [64]. The items start with “Right now I feel…” and will be continued with 1 of the following adjectives: good, bad, alertness, fatigue, relaxed, and restlessness. The participants will be able to rate them on a 5-level scale labelled from *not at all* to *very*. A slightly modified version of the trait anxiety scale of the State-Trait Anxiety Inventory [65] will be used to assess the momentary anxiety of the participants. A total of 6 adapted items are included, which can be answered on a 5-point scale, as follows: “How big do you think your fear is at the moment?”, “How much do you feel physically uncomfortable right now?”, “How strong is your need to leave the situation?”, “How tense is your feeling right now?”, “How much are you in control of the situation?”, and “How stressed do you feel?”. To our knowledge, no standardized motive-specific affect questionnaire exists so far. We therefore created an adjective list that is theoretically derived from early work by McClelland [19] and added adjectives that have been used in more recent research [66] (see the self-determination theory [67]). Participants indicated for 7 items how they feel right now by using a 7-point response scale (1, *not at all* to 7, *very much*). The items are “socially related,” “calm” (affiliation motive–specific affect; the item “relaxed” from the MDBF will also be used in the analysis for the affiliation motive), “strong,” “excited,” and “enthusiastic” (power motive), with “competent” and “self-determined” as additional items representing achievement and autonomy motive–specific affect, respectively (Multimedia Appendix 10). Construct validity of this motive-specific affect scale will be checked.

### Social Motives

Implicit social motives are measured using the PSE [60], which is the most frequently used measure to assess implicit motives. Key validity criteria are met, interrater reliability is good, and retest reliability is satisfactory [34,60]. For further discussion, refer to a previous report [21]. The PSE will be part of the online questionnaire prior to the laboratory session (for validity of the computer version of the PSE) [68]. Participants will be instructed that they will see 6 different pictures, and for each of them, they should write a fictional story with a beginning, middle, and end. The pictures will be presented for 15 seconds, and then, a text box will appear, where they can type their story. Questions that help participants to organize their stories will be presented above the pictures (eg, “What is happening right now?” and “Who are the characters?”). For each story, the participants will have 4 minutes. After 3 minutes 30 seconds, a small reminder will appear asking them to finish the story. After the 4 minutes have elapsed, the next picture will appear. The 6 pictures “couple by the river,” “nightclub scene,” “sorrow,” “beachcombers,” “NewPic32,” and “NewPic9” will be presented (Multimedia Appendix 1). As recommended previously [60], 2 experienced coders will score the stories for the power and affiliation motives according to Winter’s scoring manual [69] (interrater reliability [intraclass correlation coefficient] is expected to be between 0.80 and 0.90). Disagreements between coders will be resolved by discussion [60]. Motive scores will be corrected by word count. For further details about test administration and scoring procedure, see a previous report [60].

All participants will complete a short German version of the Bem Sex Role Inventory to screen for GRSC [61].

### Endocrine Measurements

Saliva samples will be collected for the recording of cortisol, α-amylase, and reproductive hormones. Approximately 10 mL of saliva will be dispensed through a straw into Salicaps (IBL International) (Multimedia Appendix 11). After the study, all saliva samples will be frozen and stored at −20°C. Hormone and enzyme levels will be analyzed at the stress biomarkers laboratory at the Institute of Medical Psychology, Heidelberg University Hospital.

#### Salivary Cortisol

The concentration of cortisol in saliva will be recorded in ng/mL. Seven saliva samples will be collected using Salicaps (IBL International) at measurement time points T0 (−11 min before the TSST-G), T1 (TSST-G onset), T2 (after the job interview), T3 (after the arithmetic task), and T4, T5, and T6 during the resting phase (+30 min, +45 min, and +65 min, respectively, after TSST-G onset). Cortisol will be determined with the Cortisol free in Saliva ELISA assay from Demeditec.

